**Fig. 1 Fig1:**
[figure not shown]
Flow chart for securing informed consent

#### Selection

Over a six-month recruitment period, staff from the five participating hospital wards will refer frequent users of inpatient care by completing referral forms with users’ demographic information, contact details, diagnoses, and admissions histories, extracted from patient records. As making referrals represents an additional unpaid administrative burden for already overstretched Butabika staff, Brain Gain II will offer a performance-based incentive to ward staff of 10,000 UGX (approximately $2.50 USD equivalent) for each referral form that is filled out completely and accurately. The Monitoring and Evaluation (M&E) Officer will review each form to confirm data quality before authorising a cash payment to be made directly to the staff member. Referral forms of sufficient quality will then be used to identify potential patients who meet the study criteria. Patients residing in Kampala, Jinja, Wakiso and Mukono will be eligible to receive the intervention, and patients residing elsewhere will form a comparison group.

#### Consent

The M&E Officer will assign specialised PSWs called “M&E Buddies” to visit potential participants on the hospital’s wards. M&E Buddies receive enhanced training in research procedures and ethics, including the use of the University of California, San Diego Brief Assessment of Capacity to Consent, a structured tool designed to assist research workers in assessing capacity to consent [44]. During the visit, a M&E Buddy will review the study information sheet and consent form with the participant in either English or Luganda and answer any questions.

All potential participants must assent before baseline data can be collected. Informed consent must also be secured in order for this data to be included in the evaluation. If the M&E Buddy suspects that a potential participant may not have capacity to consent, a guardian can consent as a substitute. Alternatively, a potential participant can provide informed consent at any point over a six-month follow-up period if he or she regains capacity. This provision is made to ensure that potential participants are empowered as much as possible to make their own decisions regarding participation. The process of securing informed consent is illustrated in Fig. 1.

### Peer support

All participants receive standard adult care and may have some contact with PSWs via the Recovery College. Additionally, participants in the PSW+ group receive face-to-face visits from a trained PSW. Each participant in the PSW+ group is assigned a PSW from a nearby community by an administrator in the Peer Support Office. Peer support visits are offered for up to six months after a PSW is assigned to a user. A recipient of peer support will be visited by a PSW at least once on the ward before discharge, and at least three times after discharge. For particularly vulnerable cases (i.e. three or more inpatient stays in the past 12 months), up to six visits can be made. The PSW visits occur per the recipient’s preference, either at home, at a meeting point in the community, or at the hospital when the recipient returns for outpatient visits. The carer may also be engaged in peer support visits, where possible.

The peer support visits delivered by PSWs are flexible and unstructured, and may consist of any or all of the following:
**Befriending** (social contact, supportive listening and encouragement);**Role-modelling** (sharing personal experiences of illness and recovery);**Psychoeducation** (education on recovery principles);**Problem-solving** (discussing current challenges and possible solutions, liasing with providers to resolve issues with medical and social care as needed).

The qualifications, training, supervision and compensation of PSWs as well as quality assurance for peer support visits are detailed in Table 1.

**Table 1 Tab1:** Brain Gain II Peer Support Workers

**Qualifications**	
PSWs must be adults (age 18+) with lived experience of mental or neurological disorders who are numerate, literate in at least one language and able to communicate in basic English. There is no minimum educational or professional qualification required to become a PSW.	
**Training**	
Thirty PSWs from communities in Kampala and nearby districts identified by the user-led organisation HeartSounds Uganda were trained in 2012, prior to the start of Brain Gain II. The five-day training was delivered in Kampala by three mental health professionals from the UK with experience managing peer support programmes. Training covered principles of peer support work, recovery and wellness, communications skills, techniques for managing aggression and using Tree of Life as a tool to positively reframe personal narratives of illness and recovery [31]. In March 2015 the trained PSWs participated in an additional Training of Trainers as part of Brain Gain II, to help build the capacity of new cohorts of PSWs [37]. The Training of Trainers has since been manualised and is available upon request.	
**Supervision**	
Group supervision is provided via Monthly Advisory Support Group meetings at Butabika. These meetings create opportunities for PSWs to discuss their work with one another and with Butabika staff, creating a forum for shared learning and problem-solving. If a particularly challenging medical or social issue is encountered, a PSW may request that a trusted staff member—usually a social worker or a nurse from Butabika’s Community Recovery Team—participate in the next visit. Monthly Advisory Support Group meetings are also opportunities to monitor the well-being of PSWs and provide additional support to those who are struggling. A PSW’s caseload may be redistributed to other PSWs from nearby communities, if necessary. A PSW recovering from a relapse is assessed by a psychiatrist at Butabika before resuming peer support visits.	
**Quality Assurance**	
At each visit, the PSW completes a structured follow-up form, which documents essential information such as the user’s up-to-date contact information and details about what took place. Forms are reviewed regularly by a M&E Officer to identify any inconsistencies which might suggest that a visit has not taken place, in which case an additional visit may be conducted by a Butabika staff member, to investigate.	
**Compensation**	
Although PSWs are not salaried hospital staff, they receive a lunch and travel stipend of 20,000 UGX (approximately $5 USD equivalent) for each day of activity.	

### Outcomes

For variables to be included in the primary analysis, Table 2 summarises the time-points for assessment, the form used and the data collector responsible.

**Table 2 Tab2:** Assessment of Outcome Variables and Confounders for Primary Analysis

Variable type	Variable	Assessment	Time point	Data source	Method of Assessment
**Outcomes**	• Hospital days • Rehospitalisations	Baseline	Point of referral	Secondary data from paper-based records	Data extracted from patient file and entered into referral form by ward staff, then checked by M&E Officer
		Follow-up	Six months from referral	Secondary data from paper-based records	Data extracted from patient file and entered into six-month admissions form by M&E Officer
**Confounders**	• Disability • Family support	Baseline	Initial ward visit after referral	Primary data collected via questionnaire (based on WHODAS 2.0 and MIND ME)	Reported by user to M&E Buddy using baseline form

There are two primary outcomes for this study, both related to change in frequent users’ utilisation of inpatient care at Butabika. The first is change in the number of hospital days over the previous six months. The second is change in the number of rehospitalisations over the previous six months. The index hospitalisation during which the participant was recruited into the study is excluded from both calculations. The study flow chart in Fig. 2 further illustrates the sequence of assessments in each group.

**Fig. 2 Fig2:**
[figure not shown]
Flow chart for quasi-experimental study

#### Hospital days

Hospital days are the number of days spent in psychiatric inpatient care at Butabika over the previous six months. In order to calculate the number of hospital days, dates of entry and departure are extracted from the patient file at the point of referral and six months from referral. An entry may be the result of formal admission or return to the hospital’s premises following an escape. Similarly, a departure may be the result of formal discharge or escape from the hospital’s premises.

#### Number of rehospitalisations

Number of rehospitalisations is the overall number of inpatient stays at Butabika over the previous six months. An inpatient stay is defined as a period of time spent in psychiatric inpatient care at Butabika and is also derived from the entry and departure data extracted from the patient file at the point of referral and six months from referral.

### Potential confounders

Our initial working model described in Fig. 3 suggests four confounders from previous research on risk of readmission in other sub-Saharan African countries [6, 45], two from HICs [46–50], and four proposed by the investigators: baseline values for the number of rehospitalisations and hospital days; baseline values for disability and family support; demographic factors, including gender, age, marital status, education level and employment; and diagnosis.

**Fig. 3 Fig3:**
[figure not shown]
Initial working model

However, DID is designed to adjust for time-invariant and group-invariant confounders [51]. Age, gender, diagnosis, education level, employment and marital status are unlikely to change substantially between groups within the six-month follow-up period. We also observe cautions by Glymour et al. (2005) regarding adjustment for baseline measures of outcome variables (hospital days and rehospitalisations) [52]. Therefore, we plan to include only the remaining two proposed confounders (disability and family support) as pre-specified covariates in the adjusted analysis.

The M&E Buddy collects data on these two potential confounders by administering a baseline form to the study participant while he or she is still on the hospital wards [Table 2]. For those in PSW+ group, it is completed before any PSW visits take place.

#### Disability

Disability score is assessed using the 12-item World Health Organisation Disability Assessment Scale 2.0 (WHODAS 2.0) [53]. WHODAS originated as a tool for use in psychiatric inpatient settings. WHODAS 2.0 has been validated in diverse cultural contexts and settings, and is considered to be an acceptable cross-cultural measurement tool [53–55]. A Luganda version has been developed and used in primary care settings in Uganda by the PRIME research project [56]. We will use the unweighted “simple scoring” technique manualised by Ustun et al. (2010) to calculate disability scores from the WHODAS Likert scales.

#### Family support

Family support is measured using two separate three-item Likert scales: one for family’s attitude, and one for family’s willingness to help. Face validity of these scales was examined during the development of the Mental health Information aND Monitoring and Evaluation (MIND ME) Nigeria toolkit*,* and these measures have since been integrated into routine data collection for monitoring and evaluation of three Nigerian mental health programmes [57–59]. As with the “simple scoring” technique for WHODAS, we plan to sum these Likert scales in order to produce overall family support scores.

### Bias

Although this is not a blinded study, neither M&E Buddies, PSWs or the Peer Support Office Administrator responsible for assigning PSWs have access to participants’ admissions data. Admissions data are extracted from hospital records by ward staff at baseline and by a M&E Officer at follow-up [Table 2]. To reduce the risk of bias in the collection of additional data, a participant’s M&E Buddy will not also be assigned as his or her PSW.

### Study size

Brain Gain II aims to enrol 180 users into peer support over six months. Assuming at least a 15% refusal rate and 15% loss-to-follow-up [60], we expect a maximum of 126 participants to complete follow-up in the PSW+ group. With this estimate in mind, we conducted a sensitivity analysis exploring a variety of different scenarios relating to power, effect size and intraclass correlation, allowing for both balanced and unbalanced samples, at 0.05 alpha (see Additional file 2). Results suggest it is possible to detect a clinically meaningful effect (20% as per Cohen [1998]) with 80% power, or a larger effect (30%) with 90% power, if an additional 87 users are followed up in the PSW- group [61]. We therefore aim to recruit at least 129 users to the PSW+ and 101 to the PSW- group.

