### Analysis

A detailed a priori statistical analysis plan has been drafted in consultation with a biostatistician and covers the baseline, primary and exploratory analyses described below. The plan will be finalised before any data are analysed and is available from the authors upon request. Any departures from the statistical analysis plan must be itemised and clearly justified in study reports.

We will use Stata/SE v15.1 for statistical analysis. All analyses will be performed at the level of the individual. Significance tests will be carried out with two-sided alpha of 0.05, and results will be reported with 95% confidence intervals.

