#### Missing data

We expect attrition to be low, as the primary outcome data are derived from hospital records, meaning no follow-up contact with participants is required for the main analyses. The most likely reason for missing outcome data is loss of hospital records, which is not expected to affect the study groups differentially.

As per Schafer’s (1999) guidance, we will consider up to 5 % missing data to be inconsequential [63]. However, if more than 5 % of data is missing, then we will select appropriate principled missing data methods (e.g. multiple imputation), taking into consideration the data distribution and the mechanism, rate and pattern of missing data [64].

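### The Study size figures do not fit together: 129 PSW+ recruits do not supply 126 completers at 15% loss, and the two power claims cannot share one sample and one variance

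*Protocol article*

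**What the plan says.** All the figures stand in one paragraph, Study size. The programme plans to enrol 180 users into peer support. With at least 15% refusal and 15% loss to follow-up, "we expect a maximum of 126 participants to complete follow-up in the PSW+ group". The authors then ran a sensitivity analysis over power, effect size and intraclass correlation, "allowing for both balanced and unbalanced samples, at 0.05 alpha (see Additional file 2"). They report that a 20% effect, which they credit to Cohen, can be detected "with 80% power, or a larger effect (30%) with 90% power, if an additional 87 users are followed up in the PSW- group". The conclusion is: "We therefore aim to recruit at least 129 users to the PSW+ and 101 to the PSW- group".

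The Analysis section fixes the test: "Significance tests will be carried out with two-sided alpha of 0.05". The Primary analysis subsection makes the group-by-time interaction the effect of interest, with a random effect for users who share a PSW. Both primary outcomes are numeric: change in hospital days and change in number of rehospitalisations.

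**The concern.** Three things do not agree.

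- The recruitment targets are presented as following from the completer numbers, yet 129 is only three more than 126 in a paragraph that allows for 15% loss.
- Two different effect sizes are paired with two different powers at what reads as the same sample. The gap between 20% and 30% is too wide for a step from 80% to 90% power.
- The effect is credited to Cohen without naming the scale, and on the scale most natural for numeric outcomes the claimed power is far from reached.

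The Discussion anticipates that results may be null. A reader who takes the Study size paragraph at face value would give a null result more weight against a 20% effect than the visible figures support. The PSW+ recruitment target could also be declared met with about 16 fewer completers than the power statement uses.

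**Working it through.** **Inputs from the protocol article.** Alpha 0.05, two-sided; 180 enrolled; 15% refusal; 15% loss; completers 126 and 87; recruitment targets 129 and 101; claimed power 80% for 20% and 90% for 30%. The article does not give the SD, pre-post correlation (rho), ICC or effect metric.

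**Step 1: the plan's own figure.** 180 × (1 − 0.15 − 0.15) = 126, so the 126 is reproduced by adding the two losses. Applied in sequence they give 180 × 0.85 × 0.85 = 130.

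**Step 2: recruitment against completers at 15% loss.**

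| Group | Target × 0.85 | Completers used for power | Recruits needed, n/0.85 | n × 1.15 | Loss implied by the stated pair |
|---|---|---|---|---|---|
| PSW+ | 129 × 0.85 = 109.7 | 126 | 148.2, so 149 | 144.9, so 145 | 1 − 126/129 = 2.3% |
| PSW- | 101 × 0.85 = 85.9 | 87 | 102.4, so 103 | 100.05, so 101 | 1 − 87/101 = 13.9% |

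The PSW- target matches multiplication by 1.15 and is one person short of 87, which is rounding. The PSW+ target follows from 126 by neither route and falls about 16 short. No single loss rate links both pairs. By the 1.15 rule, 129 would correspond to 112 completers (112 × 1.15 = 128.8), a number that does not appear in the text.

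**Step 3: do the two power claims fit each other?** At a fixed sample and variance, the detectable effect is proportional to z(0.975) + z(power): 1.960 + 0.842 = 2.802 at 80% and 1.960 + 1.282 = 3.242 at 90%. The ratio is 1.157, whereas 30/20 = 1.5.

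- If 20% has 80% power, then 30% has power Φ(1.5 × 2.802 − 1.960) = 98.8%.
- If 30% has 90% power, then 20% has power Φ(3.242/1.5 − 1.960) = 58%.

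Both can be true only if the variance in the second scenario is (0.3/3.242)² ÷ (0.2/2.802)² = 1.68 times that in the first.

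**Step 4: power if the effects are Cohen's d.** SE = √(1/126 + 1/87) = 0.1394 SD. The noncentral t distribution gives:

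| Completers | d = 0.2 | d = 0.3 |
|---|---|---|
| 126 + 87 | 30% | 57% |
| 110 + 86 | 28% | 55% |
| 129 + 101 (no loss at all) | 32% | 61% |

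Clustering lowers these. With about 4.2 users per PSW (126 over the 30 trained PSWs in Table 1, assuming all are active) and an ICC of 0.05 to 0.2 in the PSW+ group only, the 126 + 87 figures fall to 28–25% and 55–48%.

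**Step 5: readings that do give about 80% for the 20% effect at 126 + 87.**

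- Cohen's f = 0.2 (d = 0.4): 82%.
- Correlation r = 0.2: 84%.
- A 20-percentage-point difference in a proportion: 82–96% for a higher proportion of 0.3 to 0.8.
- A 20% relative change in a mean with coefficient of variation 0.5: 82%.
- A change score with rho of about 0.87: 80%.

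Under each of these the 30% effect has about 99% power or more, not 90%. A change score reaches 90% for d = 0.3 at rho of about 0.78, a different assumption from the 0.87.

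**Step 6: detectable effect for the planned interaction.** For a standardised change score, before clustering, the effect in baseline SD is (z sum) × √(2(1 − rho)) × √(1/n₁ + 1/n₂). At 80% power:

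| rho (assumed) | 126 + 87 | 110 + 86 |
|---|---|---|
| 0 | 0.55 | 0.57 |
| 0.5 | 0.39 | 0.40 |
| 0.7 | 0.30 | 0.31 |

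**The case against.** The strongest reply is that the power claim rests on Additional file 2, which is not shown, and an article may leave its metric, SD, ICC and correlation there. The text describes several ICC scenarios and joins the two results with an or, so each may come from its own scenario. Step 5 shows that 80% for a 20% effect is attainable on several readings. All of this stands against the flat statement, which a reader might infer from Step 4, that the design does not deliver its stated power. The documents do not show that.

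The reply does not remove the rest. Different ICCs could reconcile the two claims, but not with a small change. With clustering in PSW+ only, 30 active PSWs and an ICC of 0 in the first scenario, the 1.68-fold variance requires an ICC of about 0.52 in the second. The text mentions no such switch. No supplementary file can repair the recruitment figures either, since every number is in the one paragraph.

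It is also fair that 126 is called a maximum and 129 a minimum target, so an unseen scenario may need fewer PSW+ completers. But the power sentence adds 87 users to the 126, and the targets are then said to follow from it. If a smaller number was meant, the text should give it.

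A reader might also set the 15% loss against the Missing data section: "We expect attrition to be low, as the primary outcome data are derived from hospital records". That is a mild tension at most. A cautious planning allowance beside a qualitative expectation of few missing records is ordinary practice, and that section gives no rate that could conflict.

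**Conclusion.** The point holds in three parts of differing strength.

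- **Recruitment (firm; no outside assumption).** At the stated 15% loss, 129 PSW+ recruits yield about 110 completers against the 126 used for power. The PSW- target of 101 is sound to within one person and is not part of the finding.
- **The pair of power claims (firm under one variance).** 80% for 20% and 90% for 30% cannot both hold at 126 + 87 unless the second rests on about 1.68 times the variance of the first, which the text does not disclose.
- **The size of the power (conditional).** If the effects are Cohen's d with no large gain from the baseline measure, power is about 30% and 57% before clustering. The claim for the 20% effect cannot be reproduced from the inputs given, and reaches about 80% only under assumptions that are not stated.

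It would be tempting to offer 0.39 SD as the detectable effect of the difference-in-differences analysis. That figure applies to a comparison at follow-up alone, or to a change score if rho is 0.5. The article gives no rho, so only a range can be stated.

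**What to change.** 1. Restate the power for the planned group-by-time interaction. For each figure, name the effect metric, the pre-post correlation (or the mean and dispersion if a count model is used) and the ICC. If the 20% and 30% results come from different scenarios, say so. If a standardised change score is used, the 80%-power detectable effects in Step 6 show the form: 0.55, 0.39 and 0.30 baseline SD at 126 + 87 for rho of 0, 0.5 and 0.7, before clustering.
2. Reconcile the PSW+ numbers in one of two ways. Either base the power on the completers that 129 and 101 yield (about 110 and 86), or, if 126 completers are needed, restate the PSW+ target as 149. The 149 fits within the 180 × 0.85 = 153 consenters that the paragraph already implies.

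The cost is a short recalculation and some rewording, with a stated sensitivity that will probably look less favourable. Neither route needs enrolment beyond the programme's 180.

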### Analysis

A detailed a priori statistical analysis plan has been drafted in consultation with a biostatistician and covers the baseline, primary and exploratory analyses described below. The plan will be finalised before any data are analysed and is available from the authors upon request. Any departures from the statistical analysis plan must be itemised and clearly justified in study reports.

We will use Stata/SE v15.1 for statistical analysis. All analyses will be performed at the level of the individual. Significance tests will be carried out with two-sided alpha of 0.05, and results will be reported with 95% confidence intervals.

#### Baseline

Descriptive statistics will be tabulated at baseline for both study groups (PSW+ and PSW-) [Table 3]. The mean, standard deviation and number of observations will be presented for all continuous variables. Numbers and percentages will be presented for categorical variables. Significance tests will not be performed to test for baseline differences between the study groups, as DID already presumes that study groups are unequivalent at baseline [51].

**Table 3 Tab3:** Baseline characteristics for descriptive analysis

Variable type	Variable	Time point	Data source	Method of Assessment
**Demographic**	• Age • Gender • District of residence	Point of referral	Secondary data from paper-based records	Data extracted from patient file and entered into referral form by ward staff, then checked by M&E Officer
	• Education level • Occupational category	Initial ward visit after referral	Primary data collected via questionnaire (based on WHODAS 2.0)	Reported by user to M&E Buddy using baseline form
**Family**	• Family support • Marital status • Number of children	Initial ward visit after referral	Primary data collected via questionnaire (based on MIND ME and WHODAS 2.0)	Reported by user to M&E Buddy using baseline form
**Clinical**	• Diagnosis	Point of referral	Secondary data from paper-based records (based on MIND ME)	Data extracted from patient file and entered into referral form by ward staff, then checked by M&E Officer
	• Disability	Initial ward visit after referral	Primary data collected via WHODAS 2.0	Reported by user to M&E Buddy using baseline form
	• Years lived with mental health problem	Initial ward visit after referral	Primary data collected via questionnaire	Reported by user to M&E Buddy using baseline form
**Service use**	• Ward of referral • Hospital days • Rehospitalisations	Point of referral	Secondary data from paper-based records	Data extracted from patient file and entered into referral form by ward staff, then checked by M&E Officer
	• Previous Recovery College attendance • Satisfaction with hospital services	Initial ward visit after referral	Primary data collected via questionnaire	Reported by user to M&E Buddy using baseline form

